### Randomization

Companies participating in the study will select organizations to participate in the program. Although the coordinator will choose the organizations, if necessary, the first author and the coordinator will discuss how to select or classify the organization. The selected organizations will then be randomly assigned to the intervention or control group in a 1:1 ratio within the company unit. Permuted block randomization (block size = 2) will be adopted for equal randomization. For example, if 4 organizations in a company participate, 2 will be assigned to the intervention group and 2 to the control group. Assignments will be made after all participating employees have responded to the baseline survey (T1). All data related to randomization (company and organization lists and random number tables) will be password-protected. Research assistants not involved in program administration or results analyses and who are blind to the researchers (YK, KW, and NK) will carry out the entire randomization process. Because of the nature of the intervention, it is not possible to blind the person implementing it.

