**Methods:**

This study will be a two-arm, parallel-group cluster (organization) randomized control trial. Japanese organizations and nested employees will be recruited through the first author’s acquaintances using snowball sampling. Organizations that meet the inclusion criteria will be randomly allocated to intervention or control groups in a 1:1 ratio within the company unit. The intervention groups will be provided with a 1-month long gratitude intervention program, which aims to promote reciprocal gratitude exchanges within the same organization. The program consists of psychoeducation, gratitude lists, and behavioral gratitude expression. The control groups will not receive any intervention. The primary outcome will be work engagement measured by the Japanese version of the Utrecht Work Engagement Scale at baseline and after 1 (immediate post-survey), 3, and 6 months. Multilevel latent growth modeling will be conducted to examine the effectiveness of the intervention program.

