### Participants

This cRCT will include 2 levels: organizations and employees. The intervention program will promote interactions between employees in the same organization by expressing gratitude at each level. There will be no inclusion and exclusion criteria for organizations: any organization wishing to participate in the intervention program may do so. The inclusion criteria for individuals will be workers (1) who are more than twenty years old; (2) who belong to the organizations; (3) who work at the same organization 3 or more days a week; and (4) who have Internet access via smartphones, tablets, or computers. Temporary workers at the target organization who are also employed elsewhere will be included. Exclusion criteria for individuals will not be specified.

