### Outcomes

All outcomes will be measured using a self-reported web-based survey at baseline and at 1-month (immediate post-intervention), 3-month, and 6-month follow-ups (Table 2). All outcomes will be calculated at the individual level. The surveys will be administered simultaneously to intervention and control groups at each company.

**Table 2 Tab2:** Outcome measures

Measurement	Aim	Baseline (T1)	1-month follow-up (T2)	3-month follow-up (T3)	6-month follow-up (T4)
Primary outcome					
UWES	Work engagement	X	X	X	X
Secondary outcome					
GAWS	Gratitude at work	X	X	X	X
GSES	Sense of coherence	X	X	X	X
SOCS	Self-efficacy	X	X	X	X
BJSQ	Coworker support	X	X	X	X
	Supervisor support	X	X	X	X
TOMH well-being-24	Eudaimonic well-being at work	X	X	X	X
K6	Psychological distress	X	X	X	X
WHO-HPQ	Work performance	X	X	X	X

UWES, Utrecht Work Engagement Scale; GAWS, Gratitude At Work Scale; GSES, General Self-Efficacy Scale; SOCS, Sense Of Coherence Scale; BJSQ, Brief Job Stress Questionnaire; TOMH well-being-24, The University of Tokyo Occupational Mental Health well-being scale; K6, Kessler's psychological distress scale; WHO-HPQ; Health Performance Questionnaire

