#### Statistical analysis

Primary analysis of the intervention program’s effects on work engagement will be carried out by multilevel latent growth modeling (LGM) [53] using robust maximum likelihood estimation. This study will examine repeated measures for employees at level 1, work engagement within employees at level 2, and interactions within organizations at level 3. We will compare the significance of the dummy-variable coefficient for the intervention (control = 0, intervention = 1), with the linear slope of work engagement representing the intervention program’s effect. We will reference some model fit indices, such as χ^2^, the comparative fit index (CFI), the Tucker–Lewis index (TLI), and root mean square error of approximation (RMSEA). We will then determine the model that demonstrates a good fit based on the fit indices, specifically CFI and TLI greater than 0.95 and RMSEA smaller than 0.06 [54]. Intention-to-treat (ITT) analysis using full information maximum likelihood estimation will be conducted, including all employees who complete the baseline survey. If the LGM yields misspecified or improper solutions, we will consider running a three-level mixed-model analysis using restricted maximum likelihood estimation. If no data hierarchy is found in the organizational analysis (e.g., ICC is not significant or less than 0.05) [55], we will consider analyzing the data individually. Mplus Version 8 [56] and PASW Statistics 20 will be used for LGM and mixed model analysis, respectively. The analysis of secondary outcomes (gratitude at work, self-efficacy, sense of coherence, support from supervisors and coworkers, eudaimonic well-being at work, psychological distress, and work performance) will be conducted using the same methods. Potential subgroup analyses will be conducted, stratified by degree of commitment to the program (numbers of gratitude lists and behavioral gratitude expressions) and initial work engagement levels or gratitude at work. Some mediation analyses will also be conducted using multilevel structural equation modeling.

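### Company is the randomization stratum but is named in no analysis model; if companies differ in their change over time, the test of the intervention slope is conservative and precision is lost

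*Protocol article*

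**What the plan says.** **Allocation.** Under Randomization, organizations are "randomly assigned to the intervention or control group in a 1:1 ratio within the company unit", and "Permuted block randomization (block size = 2) will be adopted for equal randomization". Company is therefore a stratification factor, with arms balanced inside it.

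**Model.** Under Statistical analysis, the levels of the primary multilevel latent growth model are listed as "repeated measures for employees at level 1, work engagement within employees at level 2, and interactions within organizations at level 3". The effect tested is the coefficient of the intervention dummy, "with the linear slope of work engagement representing the intervention program’s effect". The fallback is a three-level mixed model, and secondary outcomes are to be analysed in the same way. Study design and setting also mentions adjustment for organization-level effects only. Company appears in none of these statements, whether as a random level, a fixed effect or a covariate.

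**Timing.** Under Outcomes: "The surveys will be administered simultaneously to intervention and control groups at each company". The two arms of one company therefore share their calendar period and whatever happens in that company during follow-up.

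**The concern.** When arms are balanced within company, a company effect adds equally to both arms and cancels from their difference. It does not contribute to the true sampling variance of the arm contrast. A model that stops at organization cannot see this. It attributes company variation to organizations and carries it into the standard error.

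Because the tested effect is on the slope, the relevant quantity is how much companies differ in their change in work engagement over the six months. Such differences are plausible: both arms of a company are surveyed together, and a reorganization or busy season in one company would move both. If they exist, confidence intervals are wider than the design warrants, the test rejects a true null less often than 5%, and precision already obtained by stratifying is not used.

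**Working it through.** **1. The protocol's own figure.** Inputs from Sample size calculation: effect size 0.30, alpha 0.05 (two-sided reproduces the figure), power 0.90, ICC 0.09, cluster size 20.

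- Two-sample t-test: 235 per arm.
- Design effect: 1 + (20 − 1) × 0.09 = 2.71.
- 235 × 2.71 = 636.85, rounded up to 637; 637/20 = 31.85, rounded up to 32 organizations per arm.

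This matches the stated 637 participants and 32 organizations per arm. The calculation uses one organization-level ICC and takes no credit for stratification.

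**2. The tested contrast: the slope.** The protocol gives no slope variances, so all components here are assumptions. Measurements are at months 0, 1, 3 and 6, with 64 organizations of 20. Organization variance is 0.045 (level) and 0.0005 (slope); employee variance is 0.6 and 0.002; residual variance is 0.3. Company level variance is 0.045 and company slope variance is varied. Organization mean slopes were compared between arms with and without company fixed effects, under a null effect, with 3,000 replicates per cell (Monte Carlo error about 0.4 points at 5%). Results for 16 companies × 4 organizations:

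| Company slope variance | Empirical SE | SE without company | SE with company | Type I without | Type I with |
|---|---|---|---|---|---|
| 0 (level differences only) | 0.0090 | 0.0090 | 0.0090 | 4.6% | 4.7% |
| equal to organization (0.0005) | 0.0090 | 0.0105 | 0.0090 | 2.3% | 5.2% |
| twice organization (0.001) | 0.0090 | 0.0119 | 0.0090 | 1.4% | 5.2% |

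In layouts of 32 × 2 and 8 × 8, type I error without company was 2.1% and 2.4% at equal variance, and 0.7% and 1.8% at twice.

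Hand check: the squared deviations of 0, 1, 3 and 6 from their mean of 2.5 sum to 21. The variance of an organization's mean slope, apart from company, is 0.0005 + 0.002/20 + (0.3/20)/21 = 0.001314. The SE of the arm difference is √(2 × 0.001314/32) = 0.0091. Leaving a company slope variance of 0.0005 in the residual gives √(2 × 0.001814/32) = 0.0106. Both agree with the simulation.

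**3. The same mechanism for a level contrast.** This uses the protocol's ICC of 0.09, 32 organizations of 20 per arm and d = 0.30. Let s be the share of the between-organization variance that lies between companies (assumed).

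- SE reported without company: √(2 × (0.09 + 0.91/20)/32) = 0.092.
- True SE under within-company balance: √(2 × (0.09 × (1 − s) + 0.91/20)/32).

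| s | True SE | Reported SE too wide by | Actual alpha | Power without company | Power with company |
|---|---|---|---|---|---|
| 0 | 0.092 | 0% | 5.0% | 90.3% | 90.3% |
| 0.25 | 0.084 | 10% | 3.2% | 92.3% | 94.6% |
| 0.50 | 0.075 | 22% | 1.7% | 94.4% | 97.9% |

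These use the normal approximation and ignore degrees of freedom spent on company.

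**The case against.** **The effect depends on an unknown variance.** This stands. The protocol gives no company-level variance, in level or in slope, and does not say whether the ICC of 0.09 contains any. If companies do not differ in trend, leaving company out costs nothing in the slope test.

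**The level-contrast error rates are not those of the primary test.** This also stands. A reader might take the 3.2% and 1.7% as the primary test's type I error. The primary test is on the slope, and company differences in level alone left its standard error unchanged.

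**Listing levels does not exclude a company covariate.** Partly right: a company fixed effect would be compatible with three random levels, and a covariate list may be left to an analysis plan. But the article itself enumerates the levels, names organization as the only cluster adjustment and repeats three levels for the fallback. As written, the model does not reflect the stratum used to randomize.

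**Odd numbers of organizations.** A reader might infer that companies will enter one or an odd number of organizations and that this biases the comparison, since "There will be no inclusion and exclusion criteria for organizations: any organization wishing to participate in the intervention program may do so". The protocol neither states nor excludes odd numbers; it lets the first author and the company coordinator discuss which organizations to select. A leftover organization that is still randomized would add noise, not bias.

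**The abstract.** Its phrase "Organizations that meet the inclusion criteria will be randomly allocated" does not fit the Participants section, but that is a wording mismatch with no bearing on whether company belongs in the model.

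**Conclusion.** The point holds as a conditional loss of precision. The analysis as described omits the factor within which organizations are randomized. If companies differ in their change over time, the standard error of the intervention effect on the slope is too wide: by about 17% (0.0105/0.0090) when company slope variance is assumed equal to organization slope variance, with type I error near 2.3% instead of 5%. If they differ only in level, nothing is lost in the slope test.

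A reader might infer that the trial is underpowered or its test invalid. The documents support neither. Type I error falls below nominal and is not inflated. The sample size took no credit for stratification, so the planned 90% power is not undercut: for the level contrast, power without company is 90.3% or more in every case shown. What is lost is extra precision and nominal coverage. The direction is secure; the size rests on assumed variances.

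**What to change.** Under Statistical analysis, state that company, as the stratification factor, is included in the primary growth model, the fallback mixed model and the secondary-outcome models. Use a random company level on both intercept and slope, or company and company-by-time fixed effects if there are few companies with several organizations each. A company term on the intercept alone would not address the slope test.

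The cost is some added model complexity. Fixed effects become expensive with many small companies: 32 two-organization companies would need 31 + 31 = 62 extra between-level parameters against 64 organizations. For the level contrast with no company variance, a simulation of that layout put power at 88.8% with company fixed effects against 89.6% without, a loss of under one point. The random company level was not simulated. In a balanced layout the arm contrast lies wholly within company, so it should give a similar standard error where company variance is estimated above zero.

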#### Statistical analysis

Primary analysis of the intervention program’s effects on work engagement will be carried out by multilevel latent growth modeling (LGM) [53] using robust maximum likelihood estimation. This study will examine repeated measures for employees at level 1, work engagement within employees at level 2, and interactions within organizations at level 3. We will compare the significance of the dummy-variable coefficient for the intervention (control = 0, intervention = 1), with the linear slope of work engagement representing the intervention program’s effect. We will reference some model fit indices, such as χ^2^, the comparative fit index (CFI), the Tucker–Lewis index (TLI), and root mean square error of approximation (RMSEA). We will then determine the model that demonstrates a good fit based on the fit indices, specifically CFI and TLI greater than 0.95 and RMSEA smaller than 0.06 [54]. Intention-to-treat (ITT) analysis using full information maximum likelihood estimation will be conducted, including all employees who complete the baseline survey. If the LGM yields misspecified or improper solutions, we will consider running a three-level mixed-model analysis using restricted maximum likelihood estimation. If no data hierarchy is found in the organizational analysis (e.g., ICC is not significant or less than 0.05) [55], we will consider analyzing the data individually. Mplus Version 8 [56] and PASW Statistics 20 will be used for LGM and mixed model analysis, respectively. The analysis of secondary outcomes (gratitude at work, self-efficacy, sense of coherence, support from supervisors and coworkers, eudaimonic well-being at work, psychological distress, and work performance) will be conducted using the same methods. Potential subgroup analyses will be conducted, stratified by degree of commitment to the program (numbers of gratitude lists and behavioral gratitude expressions) and initial work engagement levels or gratitude at work. Some mediation analyses will also be conducted using multilevel structural equation modeling.

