### Procedure

Figure 1 shows a flowchart for participants. Recruitment will be in Japan through acquaintances of the first author (YK) using snowball sampling. Many of the subjects belong to the broad community involved in the University of Tokyo’s occupational mental health field, which comprises more than 300 occupational health professionals, including doctors, nurses, clinical psychologists, and human resources management specialists from different organizations. The first author will invite them to participate in the study. If they agree to assist, the author will ask them to be a coordinator for their company and select organizations for study participation. Then, all nested employees will be recruited for the study. The employees will receive emails from the coordinator providing a program overview and ensuring its voluntary nature. The average cluster size will be approximately 20 employees. After the nested employees complete the baseline survey, organizations will be allocated randomly to the intervention and control groups. The intervention program will last 1 month. Post-surveys will be administered to both intervention and control groups immediately after intervention completion (1-month follow-up) with additional follow-ups at 3 and 6 months.

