### Control group

Participants belonging to the control group will not receive any intervention programs until they complete the 6-month follow-up survey. Then control group participants will receive the intervention program.

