### Sample size calculation

The target sample size was calculated by accounting for intraclass correlations (ICC) of the organizations’ outcomes, according to the guidelines in the Consolidated Standards of Reporting Trials (CONSORT) for cRCTs [47]. Sample sizes in cRCTs should be multiplied by design effect (1 + [m − 1]ρ), where m is the average cluster size, and ρ is ICC. In a previous study, ICC for work engagement among Japanese employees was 0.09 [48]. The cluster size was set to 20 [49]. An effect size of the individual intervention program was estimated at 0.30 based on a previous meta-analysis on well-being [39, 50]. Based on these estimations, 637 participants from 32 organizations per arm will be needed at an alpha error rate of 0.05 and a beta error rate of 0.10 using G*Power version 3.1.9.2 [51, 52].

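### The primary effect is one linear slope over six months, but the program ends at month 1 and the 90% power was computed for a 0.30 SD difference in means, so that power does not apply to the declared test

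*Protocol article*

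**What the plan says.** Under Statistical analysis, the primary analysis is a multilevel latent growth model. The effect of the program is read from the coefficient of the arm dummy, "with the linear slope of work engagement representing the intervention" program's effect. Outcomes are collected "at baseline and at 1-month (immediate post-intervention), 3-month, and 6-month follow-ups" (Outcomes). Under Procedure, "The intervention program will last 1 month", and the post-surveys come "immediately after intervention completion (1-month follow-up) with additional follow-ups at 3 and 6 months". Controls "will not receive any intervention programs until they complete the 6-month follow-up survey" (Control group).

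Under Sample size calculation, "An effect size of the individual intervention program was estimated at 0.30", "ICC for work engagement among Japanese employees was 0.09", the cluster size is 20, and 637 participants in 32 organizations per arm are required "at an alpha error rate of 0.05 and a beta error rate of 0.10". No time point is attached to the 0.30.

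Statistical analysis also sets fit thresholds (CFI and TLI above 0.95, RMSEA below 0.06). It says that a three-level mixed model will be considered if the growth model is misspecified or improper.

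**The concern.** All delivery falls in the first of the three intervals, and months 1 to 6 are untreated follow-up in both arms. A single straight line from 0 to 6 months describes a between-arm difference that grows at a constant monthly rate for five months after delivery stops. The hypothesis (engagement improves) and the sample size (a 0.30 SD difference in means) both concern a level, not a rate.

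Two things are at stake. The stated 90% power belongs to a different test from the one declared. And if the benefit wanes after month 1, the slope can be small, zero or negative even though engagement was 0.30 SD higher when the program ended. The same method is planned for every secondary outcome.

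**Working it through.** **1. The plan's own figure.** A two-sample t-test with d = 0.30, two-sided alpha 0.05 and power 0.90 needs 235 per arm. The design effect is 1 + (20 − 1) × 0.09 = 2.71. Then 235 × 2.71 = 636.85, so 637, and 637/20 = 31.85, so 32 organizations. The stated figure reproduces exactly as a comparison of means. A one-sided test (518) or 80% power (475) does not reproduce it. A single cross-sectional contrast of 0.30 SD with 637 per arm has power 0.902.

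**2. What the slope measures.** Assume calendar time scores t = 0, 1, 3, 6 and a baseline difference left free; the article states neither. The mean of t is 2.5 and Σ(t − 2.5)² = 6.25 + 2.25 + 0.25 + 12.25 = 21. The between-arm slope is Σ(t − 2.5)·d(t)/21, where d(t) is the arm difference in SD. The weights are −2.5, −1.5, +0.5 and +3.5 (each over 21), so a gain at month 1 lowers the slope.

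**3. Variance and power.** Further assumptions: 32 organizations of 20 per arm, ICC 0.09, within-person correlation r = 0.5–0.7 and cluster autocorrelation c = 0.6–1.0. The slope weights sum to zero, so the constant parts of the covariance cancel:

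SE² = (2/32) × [0.09(1 − c) + 0.91(1 − r)/20] / 21

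- r = 0.5, c = 0.6: (2/32) × (0.036 + 0.02275)/21, so SE = 0.0132 per month.
- r = 0.7, c = 1.0: (2/32) × 0.01365/21, so SE = 0.0064 per month.

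Power is from the noncentral t with 62 df.

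**4. Results for a 0.30 SD difference at month 1** (the later values are assumed):

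| Difference at months 1/3/6 | Slope per month | Over 6 months | Chance of a significant positive slope |
|---|---|---|---|
| 0.30/0.30/0.30 | 0.75/21 = 0.0357 | 0.214 | about 76–100% |
| 0.30/0.24/0.15 | (−0.45 + 0.12 + 0.525)/21 = 0.0093 | 0.056 | about 10–30% |
| 0.30/0.20/0.10 | (−0.45 + 0.10 + 0.35)/21 = 0 | 0 | 2.5% |
| 0.30/0.15/0 | (−0.45 + 0.075)/21 = −0.0179 | −0.107 | about 0% |

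Under the same assumptions the change from baseline to month 1 has 93–100% power in every row.

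**5. Break-even.** Let the difference fade linearly from 0.30 at month 1 to 0.30f at month 6. At month 3 it is 0.30(0.6 + 0.4f). The slope is zero when −1.5 + 0.5(0.6 + 0.4f) + 3.5f = 0, that is f = 1.2/3.7 = 0.32, or 0.097 SD. Above that the slope is positive but attenuated.

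**6. Sensitivity to the unstated choices.**

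- Time scores 0, 1, 2, 3: 0.30/0.20/0.10 gives +0.020 per step and 0.30/0.15/0 gives −0.015 per step.
- Baseline difference fixed at zero, compound symmetry, r = 0.5–0.8: 0.30/0.20/0.10 gives +0.012 to +0.004 per month and 0.30/0.15/0 gives −0.006 to −0.014.

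Both choices soften the result. Neither restores a contrast that corresponds to 0.30 SD.

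**The case against.** **No decay is stated.** The article predicts no trajectory, and its Background gives a mechanism (social bonds, mutual support, growing job resources) that could let the effect build after the program. On an assumed path of 0.15/0.22/0.30 the slope has 91–100% power, against 41–95% for the change to month 1. This stands: the fade patterns are assumptions, and a month-1 contrast is not better in every case.

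**A sustained effect is still found.** This also stands. With a constant 0.30 SD the slope test has 76–100% power.

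**The fit thresholds may catch the problem.** A jump followed by a fade is what a straight line fits badly. A rough single-level approximation (flat control arm, 7 df, r = 0.5–0.7) puts the population RMSEA at about 0.085–0.115 for the two steepest fades, above the 0.06 cutoff. If only misfit in the arm difference is counted, it is 0.060–0.081. So the worst cases may never reach a slope test. But the mixed model is only to be considered, its time coding and contrast are not given, and no piecewise or non-linear shape is named. If the straight line fails, the primary effect is chosen after the data are seen.

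**The analysis plan may say more.** Time scores could well be there. The linear slope, however, is not an omission: the article states it as the measure of effect.

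**A stronger reading.** A reader might infer that any 0.30 SD effect that fades gives a null or reversed result, or that the trial would often report significant harm. The documents do not support that. The sign turns only when about two thirds of the gain is lost by month 6. For 0.30/0.15/0 the linear test alone would be significantly negative in 26–79% of trials (9–70% with a common baseline mean), but that ignores the fit step and so is not the error rate of the planned procedure.

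**Conclusion.** The concern holds in a limited form. The declared primary contrast, a constant monthly rate of divergence over six months, is not the 0.30 SD difference in means that 637 per arm was sized for, so the stated 90% power does not carry over to it. The size of the loss depends on what happens after month 1. With a sustained effect the six-month slope equivalent is 0.214, or 71% of 0.30, and power remains good. With a fade to half by month 6, power drops to about 10–30%. With a fade to roughly one third or less, the slope is zero or negative.

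These figures rest on calendar time scores, a free baseline difference, no dropout, no extra random-slope variance and the correlations listed above, none of which the article gives. It does not follow that the trial will miss or reverse a real effect. What follows is that the test is poorly matched to the hypothesis, and that the contrast to be used if the linear model fails is not fixed.

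**What to change.** Before outcome data are analysed, prespecify as primary a between-arm difference in level of work engagement. Either of two routes would do:

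- A three-level model with time as a categorical factor, arm-by-time terms and a common baseline mean, which is justified because the baseline survey precedes randomization. The primary contrast is either the difference at month 1 or the mean difference over months 1, 3 and 6.
- If latent growth modeling is kept, a piecewise model with a knot at month 1, with the arm coefficient on the 0–1 month segment as the primary test.

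Report the remaining time points as prespecified maintenance effects, state to which contrast the 0.30 and the 90% power refer, and name the exact contrast to be used if the model does not fit. Apply the same to the secondary outcomes.

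The cost is analysis wording and a registry update, with the same data and software. There are two drawbacks. A month-1 contrast loses power if the effect builds slowly, which the mean over follow-ups eases: for 0.15/0.22/0.30 that mean is 0.67/3 = 0.22 against 0.15 at month 1. The mean in turn is diluted by a fade: for 0.30/0.24/0.15 it is 0.69/3 = 0.23. With a month-1 primary contrast, the six-month course also becomes a secondary statement.

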## Methods/design

### Study design and setting

This study will be a two-arm, parallel-group, non-blinded cRCT. After completing a baseline survey, randomization will be conducted at the organizational level in a 1:1 ratio for intervention and control groups. An organization refers to a structured social unit of people who are managed to meet specific needs or pursue collective goals. In this study, an organization is a group of departments, sections, or teams working together in a company. Measurements will be collected, and the intervention program’s efficacy will be analyzed, at the individual level, accounting for cluster (organization) level effects. The protocol and this manuscript were written following SPIRIT guidelines [25] and registered at the University Hospital Medical Information Network (UMIN) Clinical Trials Registry (UMIN-CTR, ID=UMIN000042546).

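### The option to analyse employees individually when the estimated ICC is non-significant or below 0.05 would ignore the unit of randomization and can lift the false-positive rate above 5%

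*Protocol article*

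**What the plan says.** Organizations are allocated 1:1 (Study design and setting), in permuted blocks of two within each company (Randomization). Study design and setting commits to an analysis of efficacy that "will be analyzed, at the individual level, accounting for cluster (organization) level effects".

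The Sample size calculation follows the same logic: "Sample sizes in cRCTs should be multiplied by design effect (1 + [m − 1]ρ"), with the statements that "ICC for work engagement among Japanese employees was 0.09" and that "The cluster size was set to 20".

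The Statistical analysis section specifies a three-level latent growth model in which the effect is the arm coefficient on the linear slope. It then adds a conditional departure for the case where no hierarchy is found at the organization level: "e.g., ICC is not significant or less than 0.05) [55], we will consider analyzing the data individually". It names no other correction for clustering in that case. Secondary outcomes are to be analysed by the same methods.

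**The concern.** Clustering in this trial comes from the allocation. Its presence is not something the data have to demonstrate. Employees of one organization always share an arm, so any correlation between them adds variance to the comparison of arms.

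- **The threshold is not negligible.** With 20 per organization, a small ICC still adds a good deal of variance.
- **Non-significance is not absence.** A non-significant ICC does not show that the ICC is zero.
- **It is a pre-test on the same data.** The organization level is dropped in those trials where the estimate happens to be low.
- **The trigger is loosely defined.** The text does not say which ICC counts (which time point, level or change), and the primary test is on the slope.
- **It can differ by outcome.** Because secondary outcomes use the same methods, clustering could be kept for one outcome and dropped for another.

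If the option is used when the true ICC is above zero in the quantity tested, standard errors are too small and a positive finding could be an artefact of ignoring the randomized unit.

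**Working it through.** **Inputs from the Sample size calculation.** Standardized effect: "An effect size of the individual intervention program was estimated at 0.30". Error rates: "needed at an alpha error rate of 0.05 and a beta error rate of 0.10". Planning ICC 0.09 and cluster size m = 20.

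**1. Reproduce the plan's figure.** A two-sample t-test with d = 0.30, two-sided alpha 0.05 and power 0.90 needs 235 per arm. The design effect is 1 + 19 × 0.09 = 2.71. Then 235 × 2.71 = 636.85, so 637 per arm, and 637 / 20 = 31.85, so 32 organizations per arm. This matches the protocol.

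**2. Individual-level test that always ignores clustering.** For a comparison of arms at one time point, with no between-company variance,

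type I error = 2 × [1 − Φ(1.96 / √(1 + (m − 1) × ICC))].

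At ICC 0.05 the design effect is 1 + 19 × 0.05 = 1.95. Then 1.96 / √1.95 = 1.404, which gives 16.0%.

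| True ICC (m = 20) | Design effect | Type I error |
|---|---|---|
| 0.01 | 1.19 | 7.2% |
| 0.02 | 1.38 | 9.5% |
| 0.03 | 1.57 | 11.8% |
| 0.04 | 1.76 | 14.0% |
| 0.05 | 1.95 | 16.0% |

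At ICC 0.05, m = 10 gives 10.4% and m = 30 gives 21.0%.

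**3. The rule as a whole.** Simulation with 64 organizations of 20 and no between-company variance. The individual t-test is used if the estimated ICC is below 0.05 or its F-test is non-significant; otherwise a cluster-level test is used.

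| True ICC | Level dropped | Type I error, rule as a whole | Type I error, level always kept |
|---|---|---|---|
| 0.01 | 99.9% | 7.1% | 4.9% |
| 0.02 | 98.6% | 9.4% | 5.1% |
| 0.03 | 91.9% | 10.8% | 5.0% |
| 0.04 | 75.0% | 11.2% | 4.9% |
| 0.05 | 52.0% | 10.2% | 4.9% |
| 0.06 | 31.0% | 8.2% | 5.0% |
| 0.09 | 3.1% | 5.4% | 5.0% |

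Repeat simulations agree within sampling error and put the ICC 0.09 value at 5.3% to 5.6%. At a true ICC of 0.05, the error among trials that drop the level is 16.5%. At 0.09 it is about 22% among the 3% that do.

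**4. Effect of blocking within company.** Assume one pair of organizations per company (32 pairs, m = 20). The split of the ICC between and within companies is not given, so a range is needed. With half of it between companies, the rule peaks at about 7 to 8%, and always ignoring clustering at ICC 0.05 gives about 10%. With 80% between companies, the rule stays at about 5.5% or below and the always-ignore figure is about 7%.

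**5. The slope.** A between-organization component that is constant over time cancels from a slope; organization-by-time variance does not. As an illustration, assume an outcome ICC of 0.05 and a within-employee correlation of 0.7. An individual-level slope test then has an error of 5% at a cluster autocorrelation of 1, 12.6% at 0.8 and 19% at 0.6. None of these correlations is in the protocol, so the figures show only that the inflation can be nil or substantial.

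**The case against.** Five points can be made for the plan.

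- **The wording is discretionary.** The ICC criterion is given as an example and the team would only consider the change. This stands as a reading of the text, and it makes the passage a conditional departure from Study design and setting rather than a flat contradiction. It does not remove the problem, because the choice would then be made after seeing the data, with no fixed trigger.
- **At the planning ICC the rule rarely fires.** At 0.09 the level is dropped in about 3% of trials and the overall error is near nominal. This stands. The larger figures need a true ICC of roughly half the planned value or less, but that is the situation the sentence is written for.
- **Blocking removes part of the ICC.** This also stands, and it lowers the figures. It does nothing about variation between organizations in the same company.
- **The primary test is on the slope.** The single-time-point figures do not carry over directly, and the slope inflation may be nil. The documents do not allow it to be sized.
- **Near-zero variances can give improper solutions.** This is a fair practical point and the fix has to provide for it.

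A reader might infer that the rule raises the false-positive rate to as much as 16%. The documents do not support that. The 16% belongs to an analysis that always ignores clustering, with a true ICC at the threshold; the rule as a whole peaks at about 11%. Nor is 16% a ceiling, since larger clusters, or a higher true ICC that is estimated low, give more.

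**Conclusion.** The concern holds. The sentence allows an analysis that disregards the unit of randomization, in tension with both the stated analysis principle and the design effect used to size the trial.

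For a single-time-point comparison with 64 organizations of 20 and no between-company variance, the average type I error under the rule is about 7% to 11% for true ICCs of 0.01 to 0.05, and about 5.5% at the planning value. If part of the ICC lies between companies the inflation is smaller, and with 80% there it largely disappears. For the primary slope test the direction is clear wherever organizations differ in change, but the size is not known. Confidence is high on the principle and moderate on the magnitude.

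**What to change.** Delete the sentence. State instead that every primary and secondary analysis accounts for the organization whatever the estimated ICC. This is done through organization-level random effects or, if those variances lie at the boundary or the solution is improper, through organization-clustered robust standard errors. Report the ICC descriptively, with no role in choosing the analysis.

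The cost is a change of wording and slightly wider intervals when the true ICC is near zero. In the simulations, always keeping the organization level held the type I error at about 5% when no part of the ICC lay between companies.
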